#### Secondary outcomes

As the PROMs are (semi-)continuous, their analysis will consist of a linear mixed model analysis. This mixed model analysis will have a random effect for each hospital, to account for the similarity of patients within a hospital. It will also have a random effect for patients within each hospital, to account for repeated measures within a patient. Fixed effects will be included in the analysis for follow-up condition, recruitment period, patient characteristics and tumour characteristics [14]. Model fit will be assessed similarly.

The EQ-5D-5L will be used to measure quality adjusted life-years (QALYs). The scores will be transformed into health utilities using the Dutch tariff [22]. The cost-effectiveness evaluation will be carried out according to the Dutch handbook for health-economic evaluations [23]. Analysis will be conducted in agreement with the intention-to-treat principle, from a societal perspective. The time horizon will be 12 months.

Healthcare costs, out-of-pocket costs of the patient and cost in the other sectors will be included (e.g., productivity losses). Hospital resource use will be taken from the hospital records, and will include all diagnostic testing, hospital visits, telephone and email consultations. Medical resource use outside the hospital, as measured using an adapted version of the iMCQ, will provide information on visits to the GP or use of paramedical care. The WAI will provide information on productivity losses due to follow-up visits. The cost associated with resource use will be derived from the Dutch handbook for costing, and tariffs and prices published by the Dutch Healthcare Authority [24]. Total costs will be calculated by multiplying resource use by integral cost prices.

As the time horizon is 12 months, neither costs nor effects need to be discounted. Incremental costs per QALY – the incremental cost-utility ratio (ICUR) – will be calculated with their 95% confidence intervals using 5,000 bootstrap replications, which will be projected on a cost-utility plane. In addition, ICUR acceptability curves will be presented and sensitivity analysis will be performed focusing on uncertainty surrounding most important cost items. To correct for potential baseline differences in patient population between the current care and the intervention group, covariate adjustment of the cost and QALY difference will be carried out.

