## Methods/design

### Study setting

The study will be conducted in six hospitals in The Netherlands. The participating centres have no previous experience with PHFU for CRC. Five hospitals are non-academic teaching hospitals (Bernhoven Hospital, Catharina Hospital, Gelre Hospitals, Jeroen Bosch Hospital, Rijnstate Hospital). One hospital is a university medical centre (University Medical Center Utrecht). The six participating centres act as clusters. The study features two conditions: condition A (in-hospital, standard-of-care follow-up) and condition B (PHFU). All six participating centres will start including patients in condition A. Three centres will perform the switch from condition A to condition B after six months of participation; the other three centres will perform the switch from condition A to condition B after 12 months of participation. The switch will be performed without a transition period. A graphical overview of the study design and setting is depicted in Fig. 1.

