### Sample size

In this SW-CRT, it is expected that the primary endpoint, the proportion of patients who had contact with the hospital regarding CRC follow-up care within the 12 months follow-up period, is approximately 100% in the in-hospital, standard of care follow-up and approximately 40% during the PHFU.

Over a realistic range of assumptions, this design has at least 80% power to detect a meaningful difference in the proportions of patients contacting the hospital. Specifically, this is the case:If at least 20 patients per six months per hospital can be included in the DISTANCE trial;If the hospital intra cluster coefficient (ICC) of the primary outcome is no more than 0.20 (typical hospital ICC are around 0.05–0.10) [12]; andIf the difference between the primary outcome in condition A and condition B is more than 40% (expected difference based on implementation in Radboud university medical center: 70%).

Of note, if 20 patients per hospital per half year will be included, then the total number of patients will be 360. Of these 360 patients, 180 will be included under condition A and 180 will be included under condition B.

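### The PROM model leaves hospital-specific change between half-years out of the standard error of the condition effect, so its intervals can be too narrow

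*Protocol article*

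**What the plan says.** The design has few clusters and few steps. Study setting states "The six participating centres act as clusters" and "Three centres will perform the switch from condition A to condition B after six months of participation"; the other three switch after 12 months. Sample size plans 20 patients per hospital per half-year.

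The PROM model is written out under Statistical methods, Secondary outcomes: "This mixed model analysis will have a random effect for each hospital, to account for the similarity of patients within a hospital", and "It will also have a random effect for patients within each hospital, to account for repeated measures within a patient". Its fixed effects are condition, recruitment period, and patient and tumour characteristics. Recruitment period is common to all hospitals.

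Fit is to be judged as for the primary outcome, whose check looks at hospital and recruitment-period averages. If fit is poor, the remedies listed there are another link, another error distribution, or covariate adjustment. None changes the random effects.

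The only ICC is in Sample size ("typical hospital ICC are around 0.05–0.10", with 0.20 as the upper limit), in a condition about the primary outcome. No ICC is given for any PROM.

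**The concern.** A single hospital intercept says that two patients of one hospital are equally alike whether recruited in the same half-year or a year apart. In a stepped wedge the condition effect is a contrast between hospital-period means. If hospitals move differently from one half-year to the next, through staffing or local practice for example, that movement adds variance to the contrast which the model does not count.

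Some movement is plausible. Condition A is each centre's own schedule, and the Discussion says local variation is accepted by design.

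The PROMs are secondary, but the last paragraph of Background counts quality of life, fear of recurrence, anxiety, depression and distress among the outcomes that together decide whether implementation succeeded. The section Other says adverse-event collection does not apply. Intervals that are too narrow could raise a false alarm about psychological harm or give false reassurance.

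**Working it through.** **The plan's own figures.** 6 hospitals × 3 half-years × 20 = 360. Condition A covers 3×1 + 3×2 = 9 hospital-periods, or 180 patients, and B the other 9, or 180. This agrees with "if 20 patients per hospital per half year will be included, then the total number of patients will be 360" and "180 will be included under condition A and 180 will be included under condition B". For the primary outcome, a 40-point difference at ICC 0.20 without drift gives power of 98% (70% v 30%) to 99.9% (100% v 60%), so "this design has at least 80% power to detect a meaningful difference in the proportions of patients contacting the hospital" holds under that model. The point below is about the PROMs only.

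**Inputs.** From the protocol: 6 hospitals, 3 half-years, 20 patients per hospital-period, assessments at 12, 18 and 24 months, and ICC 0.05–0.10 (borrowed from the primary outcome). Assumed: two-sided 5% test; correlation 0.6 between a patient's assessments; ratio R of between-period to within-period hospital correlation of 0.8 or 0.5. Total SD is set to 1. Condition is fixed per patient, so patient means suffice.

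**Formulas.**
- Variance of a hospital-period mean due to patients: s² = (1 − ICC) × f / 20, with f = (1 + 2×0.6)/3 = 0.733 for three assessments.
- Stable hospital variance: τ² = ICC × R. Hospital-by-period variance: v² = ICC × (1 − R).
- Let d₁, d₂, d₃ be the early-switching minus late-switching mean in each half-year. Only d₂ carries the condition effect. The planned model estimates it by d₂ − λ(d₁ + d₃), with ρ = τ²/(τ² + s²) and λ = ρ/(1 + ρ).
- Variance the model reports: (2/3) s² (1 + 2ρ)/(1 + ρ).
- Variance it omits: (2/3) v² (1 + 2λ²).
- Actual size: 2[1 − Φ(1.96 × SE reported / SE true)].

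**Worked case, ICC 0.10, R 0.5.** s² = 0.9 × 0.733/20 = 0.033; τ² = v² = 0.05; ρ = 0.05/0.083 = 0.602; λ = 0.376. Reported variance = 0.022 × 2.205/1.602 = 0.0303, SE 0.174. Omitted variance = 0.0333 × 1.283 = 0.0428. True variance 0.0730, SE 0.270. Size = 2[1 − Φ(1.26)] = 20.7%.

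| ICC | R | SE reported | SE true | Actual size |
|---|---|---|---|---|
| 0.10 | 0.5 | 0.174 | 0.270 | 20.7% |
| 0.10 | 0.8 | 0.176 | 0.221 | 11.8% |
| 0.05 | 0.5 | 0.173 | 0.223 | 12.7% |
| 0.05 | 0.8 | 0.177 | 0.199 | 8.1% |
| 0.02 | 0.5 | 0.168 | 0.188 | 8.0% |
| 0.02 | 0.8 | 0.172 | 0.180 | 6.2% |
| 0.01 | 0.5 | 0.164 | 0.174 | 6.5% |
| 0.01 | 0.8 | 0.167 | 0.171 | 5.6% |

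With R = 1 (no drift) the omitted variance is zero and size is 5.0%. Using only the two post-baseline assessments (f = (1 + 0.6)/2 = 0.8), the four cases at ICC 0.05–0.10 give 7.9–19.5%.

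**Simulation.** REML fits of the planned model with one value per patient (10,000–20,000 runs per setting) gave 8.6% and about 12% at ICC 0.05, and about 11% and 17–18% at ICC 0.10, for R 0.8 and 0.5. The mean estimate was within 0.005 SD of zero.

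**Condition coded to start after baseline.** With the 12-month assessment coded as unexposed and drift common to a patient's three assessments, simulated size (1,500 trials per setting) was 5.4% and 5.7% at ICC 0.05, and 5.4% and 6.5% at ICC 0.10. Analytic values were 5.2–6.1%.

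**The case against.** The strongest objection concerns baseline. PROMs are first measured at the visit that starts the study, and the model text does not say how that assessment enters. If condition is coded as starting afterwards, the patient intercept absorbs a hospital-period shift shared by all of a patient's assessments, and the inflation nearly vanishes. That stands as a limit. It does not remove the point: Outcomes compares patients by the condition under which they were included, and Other variables records the centre's condition at inclusion, so condition fixed per patient is the natural reading. Dropping baseline altogether still gives about 8–20%. Drift that appears only after baseline would not cancel either, and was not examined.

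Second, the ICC belongs to hospital contact, and the drift ratio and 5% level are not in the protocol. This also stands, and makes the range conditional.

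Third, patient and tumour covariates may absorb drift from case mix, and the fit check looks at the level where drift would show. Both help, but covariates do not remove other hospital change, and the listed remedies would not repair the standard error.

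Fourth, small-sample degrees of freedom are commonly left to an analysis plan. Agreed: their absence is not the fault here. They matter only because the added term needs them.

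A reader might infer that drift is systematically mistaken for an effect of home-based follow-up. The documents do not support that: the switch moment is randomised and the estimate is unbiased on average.

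**Conclusion.** The point holds as one about precision. The stated PROM model omits hospital-specific change between half-years, and its fit procedure offers no way to add it. Because the random effects are spelled out, this is a choice made in the protocol and not a detail lost in condensing it.

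With condition fixed per patient, a nominal 5% test has an actual size of about 8–21% at ICC 0.05–0.10 and ratio 0.8–0.5. The favourable cases belong beside that range: about 5–8% at ICC 0.01–0.02, 5% with no drift, and about 5–6% if condition starts after baseline and drift is common to a patient's assessments. It would go too far to say that the PROM tests will run at 8–21%: no PROM ICC or drift figure is available. A change is still worthwhile, because the remedy is cheap and these outcomes feed the judgement of success.

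**What to change.** In Statistical methods, Secondary outcomes, add a random intercept for hospital-by-recruitment-period to the PROM model. Base tests and intervals on small-sample degrees of freedom: Kenward-Roger, or t on about 9 df (18 hospital-periods less 6 hospital, 2 period and 1 condition parameters).

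Both parts are needed. At ICC 0.05–0.10 and ratio 0.8–0.5, with one value per patient, simulated size falls from 8.6–17.4% to 6.6–8.7% with the term and a normal reference, and to 3.5–5.4% with t on 9 df.

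The cost is one model term and no extra patients or data. Under drift, standard errors rise to about 0.20–0.27 SD from the roughly 0.18 SD the current model reports, about 10–50% larger. For ICC 0.10 and ratio 0.5, replacing s² by s² + v² = 0.083 gives ρ = 0.05/0.133 = 0.376 and an SE of √[(2/3) × 0.083 × 1.752/1.376] = 0.265, against 0.174. If there is no drift, the tests are somewhat conservative: simulated size with t on 9 df was 2.4–2.8% at ICC 0.05–0.10.

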**Methods:**

This study is designed as a stepped-wedge cluster-randomised trial (SW-CRT) in six participating centres. During the trial, three centres will implement PHFU after six months; the other three centres will implement PHFU after 12 months of inclusion in the control group. Eligible patients are those with pT2-4N0M0 or pT1-4N1-2M0 CRC, who are 18 years or older and have been free of disease for 12 months after curative surgical resection. The studied intervention is PHFU, starting 12 months after curative resection. The in-hospital, standard-of-care follow-up currently implemented in the participating centres functions as the comparator. The proportion of patients who had contact with the hospital regarding CRC follow-up between 12–24 months after curative surgical resection is the primary endpoint of this study. Quality of life, fear of cancer recurrence, patient satisfaction, cost-effectiveness and survival are the secondary endpoints.

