#### Secondary outcomes

The secondary outcomes resulting from questionnaire data will be measured at 12 months after curative surgical resection (baseline), 18 months (6 months after inclusion) and 24 months (12 months after inclusion, end of study). The following secondary outcomes result from questionnaire data:HRQoL, measured by the European Organisation for Research and Treatment of Cancer Quality of Life (EORTC QLQ-C30) Questionnaire;Fear of cancer recurrence, measured by the Cancer Worry Scale (CWS) questionnaire;Anxiety, depression and distress, measured by the Hospital Anxiety and Depression Scale (HADS) questionnaire;Utility measure, measured by the EuroQol 5-Dimension 5-Level (EQ-5D-5L) questionnaire;Extramural costs, measured by a selection of relevant questions from the Medical Consumption Questionnaire (iMCQ) from the institute of Medical Technology Assessment;Productivity losses, measured by the Work Ability Index (WAI) questionnaire.

The following secondary outcomes result from other data than questionnaire data, and will be measured over the total study period:Cost-effectiveness, evaluated by integration of the questionnaire data and data extracted from the electronic patient records;OS, evaluated by data on vital status from the NCR; andCancer-specific survival, evaluated by data from the NCR on vital status and electronic patient records.

All abovementioned parameters will be compared between patients included under condition A and condition B.

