#### Other variables

The following other variables will be collected from the electronic patient files and the NCR:Age at diagnosis;Date of resection;Date of inclusion;Centre of inclusion;Follow-up condition of centre at moment of inclusion (A or B);Participation in PHFU (yes or no);Sex (male or female);Localisation of primary tumour (according to the 3^th^ edition of the International Classication of Diseases for Oncology);Clinical and pathological TNM classification (according to the 8^th^ edition of the TNM classification);Type of surgical procedure (e.g., hemicolectomy, low anterior resection, etc.);Systemic/radiation treatment;Number of relevant comorbidities (according to the Charlson Comborbidity Index);CEA measurements; andMedical imaging reports.

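### The PROM model lists no assessment time, condition-by-time term or baseline score: on the plain reading a post-baseline effect is diluted by a third, and otherwise precision is lost

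*Protocol article*

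**What the plan says.** Under Outcomes, Secondary outcomes, the questionnaire outcomes "will be measured at 12 months after curative surgical resection (baseline), 18 months (6 months after inclusion) and 24 months". The same section ends: "All abovementioned parameters will be compared between patients included under condition A and condition B". The list under Other variables records condition once per patient, as the centre's condition when that patient was included. The abstract places the start of the intervention at the baseline time point: "The studied intervention is PHFU, starting 12 months after curative resection".

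Under Statistical methods, Secondary outcomes, the PROMs get a linear mixed model with a random effect for hospital. Of a second random effect it says: "It will also have a random effect for patients within each hospital, to account for repeated measures within a patient". The fixed part is: "Fixed effects will be included in the analysis for follow-up condition, recruitment period, patient characteristics and tumour characteristics".

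Baseline adjustment is mentioned once in that section, for the economic evaluation only: "To correct for potential baseline differences in patient population between the current care and the intervention group, covariate adjustment of the cost and QALY difference" is planned. Nothing comparable is said for the PROM scores.

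**The concern.** Recruitment period is the calendar period in which a patient entered the study. It does not distinguish that patient's 12-, 18- and 24-month scores. The listed fixed effects therefore contain nothing that separates a score taken before the intervention could act from one taken after, and nothing that uses the 12-month score as a covariate.

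The Background counts quality of life, fear of recurrence, anxiety, depression and distress among the outcomes that together decide whether implementation succeeded. It also cites an earlier single-centre study without statistically significant differences in quality of life or fear of recurrence. If a small PROM difference is going to be read as reassuring, a model that shrinks the estimate or widens its interval makes that result easier to obtain, whichever way the true effect points.

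**Working it through.** **Plan's own figures.** 6 hospitals × 3 six-month periods × 20 patients = 360. Three hospitals spend 1 period in A and 2 in B; the other three spend 2 in A and 1 in B. A: (3×1 + 3×2) × 20 = 180. B: (3×2 + 3×1) × 20 = 180. Both agree with the Sample size section. No effect size, SD or power is given for any PROM, so the SD, correlation, ICC and significance level used below are assumptions.

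**Reading 1: all three scores are outcomes and condition is constant per patient.** With complete data and a patient random intercept, the condition coefficient depends only on patient means. With effects 0, d18 and d24 at the three assessments it estimates (0 + d18 + d24)/3.

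- Sustained effect, d18 = d24 = d: 2d/3.
- Effect at 24 months only: d/3.

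These factors need no assumption about SD, ICC or correlation. In a simulation of the 6 × 3 × 20 layout (60 runs, ICC 0.05, within-patient correlation 0.6), a true sustained effect of 0.50 SD was estimated at 0.346 (Monte Carlo SE 0.024; theory 0.333). An effect of 0.50 SD at 24 months only was estimated at 0.179 (theory 0.167). Adding assessment time as a main effect alone left the sustained estimate at 0.346. Restricting the condition effect to 18 and 24 months, with time in the model, gave 0.497 (SE 0.011).

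**Reading 2: only the 18- and 24-month scores are outcomes.** The coefficient estimates (d18 + d24)/2, so there is no dilution. What is lost is the precision that the 12-month score would bring.

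**Efficiency.** Take compound symmetry, variance 1, within-patient correlation r and no clustering.

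- Mean of three scores: effect 2/3, variance (1 + 2r)/3.
- Mean of two post-baseline scores: effect 1, variance (1 + r)/2.
- The same, adjusted for baseline: effect 1, variance (1 + r)/2 − r².

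The gain from baseline adjustment is the ratio of effect²/variance.

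| r | variance, three scores | variance, two scores | variance, adjusted | gain, reading 1 | gain, reading 2 |
|---|---|---|---|---|---|
| 0.5 | 0.667 | 0.75 | 0.50 | 3.0 | 1.5 |
| 0.6 | 0.733 | 0.80 | 0.44 | 3.75 | 1.8 |
| 0.7 | 0.800 | 0.85 | 0.36 | 5.0 | 2.4 |

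Example, r = 0.6. Reading 1: z is proportional to 0.667/√0.733 = 0.778, against 1/√0.44 = 1.508 when adjusted. The ratio is 1.94, and 1.94² is about 3.75. Reading 2: 0.80/0.44 = 1.8.

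**With clustering and periods included.** The generalised least squares variance for this stepped-wedge layout was used, with r from 0.5 to 0.7, ICC from 0.02 to 0.05 and two-sided 5% (all assumed).

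| true sustained effect | power, reading 1 | power, reading 2 | power, baseline-adjusted |
|---|---|---|---|
| 0.50 SD | 44–52% | 75–81% | 94–99% |
| 0.30 SD | 19–23% | 35–40% | 55–75% |

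For 0.50 SD, the nominal 95% interval under reading 1 covers the true post-baseline effect 83–85% of the time.

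**Reading 3: condition coded as B only after baseline, with no time term.** This fits the per-patient recording of condition less well. It brings no dilution from the baseline score, but any change over time common to both conditions loads onto the condition effect. With an assumed trend of 0, 0.15 and 0.20 SD and no true effect, the simulated estimate was 0.167 SD.

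**The case against.** The strongest objection is that no sentence says the 12-month score is an outcome in the PROM model. Two post-baseline scores are also repeated measures, so the patient random effect fits either reading. The article condenses a fuller protocol, and an analysis plan may specify visit terms and baseline handling. Patient characteristics are not defined in that paragraph and might be meant to include the 12-month score.

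Much of this stands. A reader might infer that the PROM analysis is certainly biased towards no difference, or that it certainly wastes a factor of 3 to 5 in sample size. The documents do not support either as a settled fact: both hold on reading 1 only, and reading 2 has no bias. A reader might also infer that the trial's recommendation rests on a formal finding that PROMs are not worse under PHFU. The article gives no margin or decision rule for the PROMs; it only counts them among the outcomes that define success.

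The exact 2/3 also needs complete data at three correctly timed assessments. The Questionnaires section counts from PLCRC inclusion, with the first listed questionnaire at three months, while Interventions and Recruitment allow PLCRC entry at the 12-month visit. Some 12-month scores may therefore be missing or mistimed.

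What does not stand is that the point is mere silence. The article lists the model's terms, and in the same section it names baseline adjustment for costs and QALYs alone. The list of other variables contains no baseline PROM score. The listed terms are inferior to a baseline-adjusted model on every reading.

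**Conclusion.** The point holds in conditional form. As listed, the PROM model has no assessment time, condition-by-time term or baseline score. On the plain reading it estimates 2/3 of a sustained post-baseline effect, or 1/3 of an effect present only at 24 months; this rests on complete data and a condition that is constant per patient. If the 12-month score is kept out of the outcomes, the estimate is unbiased but forgoes a gain worth about 1.5 to 2.4 times the sample size. The corresponding range on the plain reading is 3.0 to 5.0. Those multiples depend on assumed correlations of 0.5 to 0.7 and ignore clustering.

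Dilution shrinks harm and benefit alike and describes the expected estimate; a chance baseline imbalance could move a single result either way. The text does not settle which reading applies, so this is a worthwhile correction to secondary analyses and not a fundamental flaw. The primary endpoint, its model and N = 360 are unaffected.

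**What to change.** State whether the 12-month score is an outcome or a covariate, and rewrite the PROM model in one of two ways:

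- Model the 18- and 24-month scores as outcomes, with fixed effects for 12-month score, assessment time, condition, condition-by-time and recruitment period, and the random effects already planned.
- Or keep all three scores as outcomes in a constrained-baseline model, with a common 12-month mean and condition effects only at 18 and 24 months. This retains patients whose 12-month score is missing, which matters given entry to PLCRC at the 12-month visit.

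Name the condition effect averaged over 18 and 24 months, or the effect at 24 months, as the PROM estimate. Adding assessment time as a main effect alone is not enough. The planned patient and tumour characteristics can stay in either model.

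The cost is analysis wording, settled before the outcome data are examined. Baseline scores are already among the planned measurements, although the questionnaire timetable counted from PLCRC inclusion should be reconciled with the one counted from resection, so that it is clear which questionnaire supplies the 12-month score. No change to recruitment, sample size or the primary analysis is needed.

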A systematic review by Jeffery et al. focused on the different follow-up strategies for non-metastatic CRC patients, and showed that intensive follow-up was associated with fewer interval recurrences (relative risk [RR]: 0.59, 95% CI: 0.41; 0.86) and that the rate of salvage surgery increased with intensive follow-up (RR: 1.98, 95% CI: 1.53; 2.56). They however concluded that there is no evidence for OS benefit for intensified follow-up after curative surgical resection (hazard ratio: 0.91, 95% confidence interval [CI]: 0.80; 1.04) [10]. Several large randomised controlled trials were included in this systematic review, such as the CEAwatch trial, [13] the FACS trial, [14] the COLOFOL trial, [15] and the GILDA trial [16]. Combined, abovementioned studies have provided the scientific basis for the present Dutch guideline on CEA-guided follow-up for curatively treated stage I-III CRC patients.

A narrative review by Qaderi et al. showed that hospital-based CRC follow-up is common and associated with high patient satisfaction, but that there is also a willingness of patients and health care providers for alternative CRC follow-up, including general practitioner-led or patient-led, home-based follow-up (PHFU) [17]. Qaderi et al. studied the implementation of such a PHFU plan at the Radboud university medical center, Nijmegen, The Netherlands [18]. One year after implementation, no statistically significant differences in health-related quality of life (HRQoL) or fear of cancer recurrence were found. Patient satisfaction with the PHFU plan was rated with a mean of 7.5 out of 10 (standard deviation: 1.3). Also, the PHFU showed a considerable cost-saving compared to the previous follow-up plan, i.e., a total cost of €14,880 versus €37,288 per year for the included patients (*N* = 118). Both studies by Qaderi et al. showed that there is a clear potential for PHFU. Accordingly, extension of scientific knowledge on this setting of CRC follow-up is desirable. This knowledge can be generated by means of an implementation trial of PHFU for CRC in a research setting.

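### As described, the cost-utility comparison carries no recruitment-period or hospital term, and its bootstrap interval on the ICUR cannot be read if the QALY difference is near zero

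*Protocol article*

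**What the plan says.** The Protocol article sets out three analyses under Statistical methods.

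- **Primary outcome:** a mixed model with a random hospital effect and fixed effects for condition and recruitment period.
- **PROMs (Secondary outcomes, first paragraph):** the same two terms, plus a random patient effect and patient and tumour characteristics.
- **Cost-utility (Secondary outcomes, last paragraph):** the stated purpose of adjustment is to correct for imbalance between the two patient groups at baseline, and for that purpose "covariate adjustment of the cost and QALY difference will be carried out". No covariates are listed, and neither period nor hospital is named. The costs per QALY "will be calculated with their 95% confidence intervals using 5,000 bootstrap replications", with no resampling unit given. The replicates go on a cost-utility plane, and acceptability curves and sensitivity analyses are added. The horizon is 12 months.

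On the likely size of the QALY difference, the only evidence is in Background: in the single-centre implementation study, "no statistically significant differences in health-related quality of life (HRQoL) or fear of cancer recurrence were found". The aims at the end of Background list cost-effectiveness among the outcomes that together decide whether implementation succeeded.

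**The concern.** In a stepped wedge, condition is tied to calendar time by design. The protocol handles this for the primary outcome and the PROMs. The cost-utility text reasons like a two-group comparison, in which baseline patient differences are the only imbalance to remove. Adjusting for patient characteristics does not remove a change over time in how much care is used or in reported utility. Such a change would be read as an effect of PHFU.

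The second matter is the interval on the ratio. When the QALY difference is small relative to its standard error, bootstrap replicates fall on both sides of zero. The ratio then jumps from large negative to large positive values. Percentiles of that mixture do not order outcomes from worse to better, so they do not work as a confidence interval. A clear cost saving could be hidden behind an interval that seems to say nothing is known.

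**Working it through.** **1. Layout and the protocol's own totals.** All six hospitals start under A, and Study setting gives the switch times as follows: "Three centres will perform the switch from condition A to condition B after six months of participation; the other three centres will perform the switch", in this second group at month 12. Sample size adds that "if 20 patients per hospital per half year will be included, then the total number of patients will be 360", which implies three half-year periods: 6 × 3 × 20 = 360. Three hospitals follow A-B-B and three A-A-B, giving 9 A cells and 9 B cells of 20 patients. That is 180 and 180, as stated ("180 will be included under condition A and 180 will be included under condition B"). The power statement covers the primary outcome only.

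**2. Condition against time.** The share of patients under B is 0%, 50% and 100% in periods 1, 2 and 3. With even recruitment, the period midpoints are months 3, 9 and 15.

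- A: (120 × 3 + 60 × 9)/180 = month 5
- B: (60 × 9 + 120 × 15)/180 = month 13
- Gap: 8 months, so 8/12 = 0.67 of a yearly trend enters an unadjusted difference (1.33 half-year periods)
- Correlation of condition with period: 0.82

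**3. What a trend would do to the cost difference.** The single-centre figures in Background give a saving of (37,288 − 14,880)/118 = EUR 190 per patient. The cost SD of EUR 500, the drift and the ICC are assumptions. The expected unadjusted difference is −190 + 1.33 × drift per period. Simulation (4,000 runs) at ICC 0.05:

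| Drift per half-year | Expected, unadjusted | Simulated, unadjusted (coverage) | With period and hospital (coverage) |
|---|---|---|---|
| EUR 0 | −190 | unbiased (92%) | – |
| EUR −50 | −257 | −255 (72%) | −189 (95%) |
| EUR −100 | −323 | −322 (31%) | −187 (96%) |

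At ICC 0, coverage of the unadjusted interval is 95%, 76% and 28% in the three rows.

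**4. Precision.** For a unit SD, the two-group standard error is √(2/180) = 0.105. In the standard stepped-wedge variance formula with fixed periods and a random hospital effect, it is 0.183 at ICC 0 and 0.206 at ICC 0.05. The ratios are 1.73 and 1.95, so variance rises by a factor of 3.0 to 3.8.

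**5. The ratio interval.** Assume a QALY SD of 0.10 to 0.20 and a true gain of 0 to 0.02.

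| Quantity | Without the terms | With period and hospital (ICC 0.05) |
|---|---|---|
| SE of QALY difference | 0.011–0.021 | 0.021–0.041 |
| Gain/SE (z) | 0–1.90 | 0–0.97 |
| Replicates with a QALY difference below zero | 3–50% | 17–50% |

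The 95% Fieller set for a ratio is bounded only if the denominator's z exceeds 1.96, and here it does not. Nine example trials were simulated without the terms (QALY SD 0.15, gain 0 to 0.01, saving EUR 190). In eight, the percentile interval crossed zero, for example EUR −196,000 to +181,000 per QALY, while 99 to 100% of replicates showed a cost saving. With a gain of 0.05, all three example intervals had one sign, for example EUR −8,500 to −1,300.

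**The case against.** A reader might infer that the cost-utility result is time-confounded and its interval meaningless. The documents do not support that, for five reasons.

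- **Bias needs a trend, and none is documented.** The guideline revision that reduced imaging dates from December 2020, and inclusion began in July 2022. With no trend, no bias enters.
- **The covariates and resampling unit are unstated.** Period and hospital are not expressly excluded, and a fuller document may name them. So it cannot be said that the bootstrap ignores clustering.
- **Standard unit prices are used.** Costs are resource use multiplied by handbook prices and published tariffs. This largely removes price and hospital price-level effects and leaves trends in resource use.
- **The hospital mix is chance imbalance.** Early-switching hospitals supply 1/3 of A and 2/3 of B, but switch time is randomised. This is mainly a matter of precision.
- **A near-zero QALY difference is an inference.** A non-significant result in one centre is not an expected difference of zero. The plane and acceptability curves remain usable near a zero denominator.

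All five stand, and they limit the point without removing it. What the paragraph does state is an adjustment with a narrower purpose than the one beside it. The PROM model does not fill the gap: costs are not PROMs, and that model is built for repeated scores rather than one QALY total per patient. The interval on the ratio is a stated commitment, not an omitted detail. The plane and curves are drawn from the same replicates, so any bias carries into them.

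**Conclusion.** The point holds in a limited form. As described, the cost and QALY differences are open to confounding by any secular trend in resource use or utility: about 0.67 of a yearly trend would enter, and none if there is no trend. Their standard errors would be smaller than those of a model with period and hospital by a factor of 1.73 to 1.95 (ICC 0 to 0.05). The interval on the ICUR is not interpretable if the QALY difference is near zero. That is plausible from the single-centre result and the 12-month horizon, but the protocol does not state it. If the true gain were as large as 0.05, an interval without the two terms could be usable.

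The month 5 and 13 figures rest on the stated recruitment rate and even accrual. The cost SD, QALY SD, drift and ICC for costs and QALYs are assumptions. This concerns a secondary outcome and leaves the primary analysis untouched, but cost-effectiveness counts towards the judgement of success.

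**What to change.** State that incremental costs and incremental QALYs, the latter adjusted for baseline utility, are estimated with condition, recruitment-period fixed effects and a hospital effect. State that each bootstrap replicate refits this model, with resampling that respects the hospital-by-period structure. Resampling within cells does not by itself deal with clustering, so the model terms have to. Six hospitals are too few to rely on resampling whole hospitals.

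Report incremental costs, incremental QALYs and incremental net monetary benefit with 95% intervals across the threshold range, alongside the planned plane and acceptability curves. These replace the confidence interval on the ratio. Make this a fixed rule, not one triggered by whether the observed QALY interval includes zero, so that reporting does not depend on the data.

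The change needs no new data. It costs wider intervals, with standard errors about 1.7 to 2 times those of the two-group comparison, and a little more analysis work.
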